**5.1.3. Concomitant Medication**

In the present trial the only medications that cannot to be used are the ones that have an antimalarial activity, i.e. amodiaquine, chloroquine and tetracyclines.

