Because of the above failures, the PNG medical authorities have planned to introduce gradually a new artemisinine derivative to replace quinine and Fansidar, which is the present standard regimen for complicated or resistant malaria. At present, the main problem is not the lack of potent drugs, but the lack of potent and cheap drugs. Indeed, the combination of atovaquone and proguanil (Malarone), or more recently the combination of benflumetol and artemether (Riamet) have proved to be safe and efficacious, but they are unaffordable for people living in endemic areas. Mefloquine (Lariam) has proved to be quite efficacious for a while in South East Asia against multiresistant falciparum malaria, and also reasonably cheap. In the last decade, treatment failures have become more frequent and artemeter was added in combination with mefloquine to the standard treatment regimen for falciparum malaria in multidrug resistant areas of Thailand (Price et al, 1995). It is possible that a fixed combination (artemisinine derivative + mefloquine) will be available in the future to fight multiresistant parasites in highly endemic areas. In this context, testing mefloquine alone in PNG is a step towards the development of safe and efficacious drugs and drug combinations for the country when quinine and Fansidar will not be sufficient anymore.

In the same sense, the development of Cotrifazid is promising. Indeed it meets most of the requirements for a new drug for resistant malaria, which are the following : it is a combination made of relatively short-acting compounds (decreasing the rapid spread of resistant strains) ; it is active against resistant strains of *Plasmodium falciparum* in vitro and it is efficacious in mice infected with resistant strains (Brun *et al*., unpublished data) ; it is likely to be safe since the compounds have been used either alone or in combination for a very long time for the treatment of tuberculosis for example, with higher dosage for a much longer duration ; it is likely to be cheap (approx. 5 dollars for a full treatment).

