The rationale to use this combination is based on animal and human experiments. Rifampicin is active against *Plasmodium berghei* malaria in rodents (Alger et al, 1970 ; Brun, unpublished data). Numerous studies showed co-trimoxazole to be efficacious in the treatment of malaria in humans (Bloland et al, 1991 ; Hansford et al, 1982 ; Hutchinson & Farquhar, 1982). There is a pharmacokinetic synergism between co-trimoxazole and rifampicin, with increase of t50 and AUC when administered simultaneously (Bhatia et al, 1991). Isoniazid has no clear anti-plasmodial activity. It has only been shown to delay malaria mortality in mice, and to reduce overall parasite load when given in combination with rifampicin and co-trimoxazole (Brun, unpublished data). This may be due to an effect of isoniazid on blood cytokines, in particular TNF-alpha, since isoniazid did protect mice against endotoxin lethality (Urbaschek et al, 1991). The last argument to include isoniazid in the combination is to avoid the selection of resistant mycobacteria when treating for malaria an undiagnosed tuberculous patient. This risk has been revisited recently, and clear-cut evidence was presented that such a event was extremely improbable (Mueller-Brundaler et al, 1997). Even WHO, when defining a case of ‘previously untreated’ pulmonary tuberculosis for the purpose of an eventual ‘primary drug resistance’ identification, accepts for such a patient a previous antituberculous chemotherapy of up to 1 month duration (WHO, 1997). This is based also on the experience that, even with rifampicin monotherapy, the probability of selecting for rifampicin resistance of tubercle bacilli is very low. Moreover, should one fear the possibility of a not recognized advanced pulmonary tuberculosis case receiving Cotrifazid for malaria, then isoniazid as the usual combination drug for treatment of that disease would offer an additional protection against the selection of rifampicin-resistant bacilli.

Study area

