**2 GENERAL DESIGN**

**2.1 Overall Design**

This is an open, block-randomised, comparative, multicentric study.

All subjects presenting at the outpatient clinic or admitted in the ward of the Maprik Hospital and Yagaum Health Center who are diagnosed with malaria (history of fever and no other major symptom, OptiMAL test positive) and have been already treated for malaria in the last 28 days can be included if they give their informed consent and if the clinician in charge would have given the standard treatment for resistant malaria in the absence of the study. A patient should not be included if the clinician prefers to use quinine for whatever reason, if the patient has one of the symptoms or signs of complicated or severe malaria (i.e. history of recent convulsion, any neurological sign or impairment of consciousness, temperature >40 C0, heavy vomiting, haemoglobinuria, respiratory distress, bleeding, circulatory collapse, shock, jaundice, haemoglobin < 5 g/dl), has contra-indications for mefloquine (history of psychiatric disorder, epilepsy), is less than 6 months of age, or is pregnant. The patients will be randomised on the spot to have either Cotrifazid, Lariam or standard treatment (at present quinine + Fansidar). The treatment dosage and schedule for Cotrifazid will be the following : subjects > 40 kg : 2 x 2 tablets, subjects < 40 kg and > 20kg : 2 x 1 tablet, subjects < 20 kg : 2 x ½ tablet, ever 12 hours for 7 days. The treatment dosage and schedule for Lariam will be the following : subjects > 60 kg : 6 tabs (3 at hour 0, 2 at hour 8, 1 at hour 24), subjects > 40 kg and < 60 kg : 5 tabs (2, 2, 1), subjects < 40 kg and > 30 kg : 3 ½ tabs (1 ½ , 1, 1), subjects < 30 and > 20 kg : 3 tabs (1, 1, 1), subjects < 20 kg and > 10 kg : 1 ½ tabs ( ½ , ½, ½ ), subjects < 10 kg : ¾ tablet ( ¼ , ¼, ¼ ). Follow-up assessments will be done at hours 24, 48 and 72 (clinical, parasitological and pharmacological), and days 7 (clinical, parasitological, biochemical, and pharmacological) and 14 (clinical, parasitological, haematological, and pharmacological), or more intensively in case of persisting symptoms or pathological signs. Treatment will be changed to the standard treatment (at present quinine + Fansidar) if necessary (problems of tolerance, aggravation of clinical status, increase in parasitaemia etc).

All blood samples will be taken by venepuncture (2 ml).

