**4.1 Names and Formulations**

Cotrifazid is a combination made of rifampicin 112.5 mg, sulphamethoxazole 200 mg + trimethoprim 40 mg, and isoniazid 75 mg.

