## In this study AEs will be measured against the medical history, baseline physical examination and laboratory baseline values.

## AEs should be described by severity, intensity and relationship to the compounds under study as well as the method by which the information was obtained (observed, elicited or spontaneously reported).

The severity/intensity of adverse events is graded on a 3-point scale as follows:

**MILD:** Discomfort noted, but no disruption to normal daily activities.

**MODERATE:** Discomfort sufficient to reduce or affect normal daily activities.

**SEVERE:** Inability to perform normal daily activities.

**All** adverse events encountered during the clinical trial will be reported in the case report form.

An **adverse event** is defined as any adverse change from the subject's baseline pre-treatment condition (signs and symptoms at baseline), which occurs after chemotherapy has started, whether considered related or not to the drug. This includes clinically relevant laboratory abnormalities and intercurrent illnesses which occur or worsen during the study period.

The intensity of adverse events will be graded on a three-point scale (mild, moderate and severe) and described in detail, along with the investigator's assessment of the relationship of the event to treatment.

The investigator's assessment of the event's relationship to the trial treatment should be defined according to the following standard statement:

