**5.3 Assessment of Efficacy**

**5.3.1 Primary Efficacy Parameters**

The primary parameters of efficacy i) fever clearance time, ii) parasite clearance time, iii) failure rate, iv) occurrence of complications, information collected from day 1,2,3, 7 and 14.

Thick and thin blood films will be Giemsa stained and species-specific density will be counted per/200 white blood cells (WBC). Slides will be declared negative if no parasites are seen in 100 thick film fields. Parasite density per microliter blood will be calculated by multiplying the parasitemia/200 WBC by a WBC count of 10000/L in children aged < 5 years and of 8000/L in persons aged > 5 years.

1. **Secondary Efficacy Parameters**

The secondary parameters of efficacy are i) symptom clearance time, information collected at day 1,2,3, 7 and 14, and ii) haemoglobin concentration from samples collected at day 14.

1. **Assessment of Pharmacology**

Pharmacokinetics will be assessed in a small subsample of patients (5). Blood will be drawn (2 ml by venepuncture) at hour 2, 8, 16, 24, 36, 72.

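### Section 5.1.3 bars drugs with antimalarial activity but closes the class with a list that omits co-trimoxazole, an antimalarial by the protocol's own account and a component of Cotrifazid

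*Protocol*

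**What the plan says.** The whole concomitant-medication rule is one sentence in Protocol section 5.1.3: "the only medications that cannot to be used are the ones that have an antimalarial activity, i.e. amodiaquine, chloroquine and tetracyclines".

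Three other places bear on it.

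- **Activity.** Section 1.1, giving the rationale for the combination, states: "Numerous studies showed co-trimoxazole to be efficacious in the treatment of malaria in humans".
- **Composition.** Section 4.1 states: "Cotrifazid is a combination made of rifampicin 112.5 mg, sulphamethoxazole 200 mg + trimethoprim 40 mg, and isoniazid 75 mg". The sulphamethoxazole and trimethoprim together are co-trimoxazole.
- **Occasion for use.** Section 5.2.2 expects illnesses other than malaria to arise during follow-up. Of its adverse event definition it says: "This includes clinically relevant laboratory abnormalities and intercurrent illnesses which occur or worsen during the study period".

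One use of antimalarials beyond the initial allocation is planned. Section 2.1 says: "Treatment will be changed to the standard treatment (at present quinine + Fansidar) if necessary".

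**The concern.** The rule has two halves, and for co-trimoxazole they give different answers. The first half bars whatever acts against malaria. The second half, introduced by *i.e.* and governed by *only*, reads as the complete list. Because that list includes one antibacterial class, the tetracyclines, a reader may conclude that antibiotics were considered and that the others are allowed.

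The main hypothesis in section 10.1 is that the cure rate with Cotrifazid is not inferior to that with mefloquine or with quinine and Fansidar. Co-trimoxazole given on top of a comparator would supply an active component of the test product. Given on top of Cotrifazid, it would add to the dose of one. Either could change whether a patient counts as cured. Section 4.2 makes the trial open, so such use could also differ between arms. Staff apply this rule at the point of care, so a later analysis document cannot repair it.

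**Working it through.** The plan states no figure on this point, so the check is mainly a comparison of texts.

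**Step 1: is co-trimoxazole in the class?** Yes. Section 1.1 describes it as efficacious in human malaria, and section 4.1 shows it was chosen as part of the antimalarial under test.

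**Step 2: is it on the list?** No. The list has amodiaquine, chloroquine and tetracyclines.

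**Step 3: does other text extend the list?** No. Section 3.3 sets conditions for entry, not for drugs given afterwards. Section 6.1 allows withdrawal for intercurrent illness but does not say which drugs may treat it. Section 2.1 covers only the switch to standard treatment.

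**Step 4: the two readings side by side.**

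| Drug given for an intercurrent illness | Read by the class | Read by the list |
|---|---|---|
| A tetracycline | barred | barred |
| Co-trimoxazole | barred | allowed |

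**Step 5: can the direction of a bias be fixed?** Take the rates in the sample size paragraph of section 10 as if they were true: 95% success on a comparator and 86% on Cotrifazid, a difference of 9 points. Assume, purely to test the sign, that extra co-trimoxazole turns a share *q* of failures into successes. The documents give no value for *q*. The failures available to convert are 5% on a comparator and 14% on Cotrifazid, so the observed difference (comparator minus Cotrifazid, in points) becomes:

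- same *q* in both arms: (95 + 5*q*) − (86 + 14*q*) = 9 − 9*q*
- comparator arm only: (95 + 5*q*) − 86 = 9 + 5*q*
- Cotrifazid arm only: 95 − (86 + 14*q*) = 9 − 14*q*

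| Assumed *q* | Both arms | Comparator only | Cotrifazid only |
|---|---|---|---|
| 0.1 | 8.1 | 9.5 | 7.6 |
| 0.2 | 7.2 | 10.0 | 6.2 |
| 0.3 | 6.3 | 10.5 | 4.8 |

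The difference shrinks in two patterns of use and grows in the third. The protocol says nothing about which pattern to expect, so the sign is open. The table shows a mechanism and does not estimate an effect.

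**The case against.** The best defence is that the general clause already gives the right answer. Co-trimoxazole plainly acts against malaria by the protocol's own account, so a careful site would see that it is barred. The English of the sentence is rough, and *i.e.* may be a slip for *e.g.* This has force and is the main reason for a minor rating. It does not remove the defect, because the sentence as printed defines the class by its list and two sites could apply it differently in good faith.

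Exposure is also limited. Section 3.2 requires no other major symptom or sign at entry, and section 6.1 makes intercurrent illness a ground for withdrawal. Nothing shows that co-trimoxazole use would be common. Neither provision bars the drug, however.

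A reader might infer stronger points that the documents do not support.

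- **Quinine, Fansidar and mefloquine as equal omissions.** Section 1.1 does call them antimalarials ("quinine and Fansidar, which is the present standard regimen for complicated or resistant malaria" and "Mefloquine (Lariam) has proved to be quite efficacious for a while in South East Asia against multiresistant falciparum malaria"), and the list omits them. But they are trial treatments, governed largely by allocation, the dosing rules and the planned switch. Quinine with Fansidar cannot be barred outright, because it is the replacement treatment.
- **Contaminated patients stay in the efficacy population because of this list.** Section 9 selects on doses received and a follow-up visit. A patient given chloroquine, which is on the list, would stay in as well. Lengthening the list changes nothing there.
- **Co-trimoxazole use could never be a protocol deviation.** Section 6.1 does not define deviations, and under the class wording it would be one.

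**Conclusion.** Section 5.1.3 is wrong as written, with minor severity. Its closed list contradicts its own class for co-trimoxazole, so the answer at the bedside depends on which half of the sentence the site follows. This conclusion rests on the text alone: the protocol's description of the drug as efficacious, its presence in Cotrifazid, and the absence of any wording that extends the list.

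The consequence is a possibility only. Cure outcomes in the non-inferiority comparison could be altered if co-trimoxazole were given outside the assigned treatment. The documents give no rate of such use, no effect of it and no pattern by arm, so neither the size nor the direction of a bias can be derived. A reader might take the defect to favour a finding of non-inferiority. That holds only under particular patterns of use, and the protocol supports none of them over another.

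**What to change.** Replace the sentence in section 5.1.3 with:

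> Apart from the assigned treatment and the protocol-specified change to standard treatment, no drug with antimalarial activity is to be used up to day 14, including amodiaquine, chloroquine, tetracyclines, co-trimoxazole and any non-assigned trial drug. If one is needed for care it is given, and drug, dose and date are recorded.

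The opening exemption is needed because a class rule without it would literally cover the trial treatments themselves and the planned switch. The word *including* makes the class govern and the names serve as examples. The closing sentence ensures that no patient is denied necessary treatment and that any exposure is on record.

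The cost is one amended sentence, one added sentence and the recording of any such use. The small downside is that sites use another antibiotic where one is suitable.

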**5.2 Assessment of Safety**

**5.2.1 Safety Parameters (including Laboratory Evaluations)**

The prime measurement of safety in this trial is the close observation of the subjects. All subjects will be followed clinically every day for the first 4 days, and longer in case of complication. All subjects will be seen at day 7 and 14 to identify late adverse events or clinical failure.

Laboratory measurements : AST and ALT will be measured at Day 0 and 7, haemoglobin concentration at day 14.

## 5.2.2 Adverse Events

An adverse event is **ANY** type of adverse change from the trial subject's pre-drug baseline condition. **ALL** adverse events MUST be reported by the investigator without 'filtration', whether considered treatment-related or not. The wording used in English will be drawn from a list of preferred terms, with their closest equivalent in pidgin.

## In this study AEs will be measured against the medical history, baseline physical examination and laboratory baseline values.

## AEs should be described by severity, intensity and relationship to the compounds under study as well as the method by which the information was obtained (observed, elicited or spontaneously reported).

The severity/intensity of adverse events is graded on a 3-point scale as follows:

**MILD:** Discomfort noted, but no disruption to normal daily activities.

**MODERATE:** Discomfort sufficient to reduce or affect normal daily activities.

**SEVERE:** Inability to perform normal daily activities.

**All** adverse events encountered during the clinical trial will be reported in the case report form.

An **adverse event** is defined as any adverse change from the subject's baseline pre-treatment condition (signs and symptoms at baseline), which occurs after chemotherapy has started, whether considered related or not to the drug. This includes clinically relevant laboratory abnormalities and intercurrent illnesses which occur or worsen during the study period.

The intensity of adverse events will be graded on a three-point scale (mild, moderate and severe) and described in detail, along with the investigator's assessment of the relationship of the event to treatment.

The investigator's assessment of the event's relationship to the trial treatment should be defined according to the following standard statement:

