**10.4.2 Primary Safety Parameters**

Rates of acute and subacute AEs by severity and relation to the drug will be compared between the Cotrifazid and the comparator groups. Laboratory parameters (haematological) in the two groups will be compared.

The Mantel-Haenzel Chi-square test (x2=0.05, two-tailed) will be used to assess any significant difference between the two groups in terms of number of AEs reported.

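### Adverse-event severity is graded only by discomfort and daily activities, so a symptom-free AST/ALT rise of any size cannot appear as moderate or severe in the safety comparison

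*Protocol*

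**What the plan says.** Section 5.2.2 introduces the scale with "The severity/intensity of adverse events is graded on a 3-point scale as follows". The three grades are:

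- The lowest grade, MILD, is worded "Discomfort noted, but no disruption to normal daily activities".
- The middle grade, MODERATE, is for discomfort that limits what the patient usually does.
- The highest grade, SEVERE, is worded "Inability to perform normal daily activities".

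The adverse-event definition in the same section extends to laboratory findings: "This includes clinically relevant laboratory abnormalities and intercurrent illnesses which occur or worsen during the study period". Section 5.2.1 schedules the measurements that could produce such events: "AST and ALT will be measured at Day 0 and 7, haemoglobin concentration at day 14".

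Section 10.4.2 plans a comparison between arms of "Rates of acute and subacute AEs by severity and relation to the drug". Its one named test for adverse events, a two-tailed Mantel-Haenszel chi-square, is applied to the number of events reported. For laboratory parameters it names only haematology. The synopsis, under tolerance in its statistical analysis, lists a comparison of both biochemical and haematological results.

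Section 5.2.3 separately allows an abnormal laboratory value in the treatment period that points to a significant hazard to be an immediately reportable adverse event.

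**The concern.** The scale measures how the patient feels and functions. A liver-enzyme rise can be large in a patient who notices nothing. The protocol admits that finding as an adverse event but then grades it on an axis that carries no information about it. A small rise and a very large one receive the same grade, or none.

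Safety of Cotrifazid is one of the two study hypotheses (section 10.1), and the comparison by severity belongs to the primary safety analysis. If one drug caused more large silent rises than another, the moderate and severe rows could not reflect it. The trial is also open (section 4.2) and 5.2.2 sets no threshold for clinical relevance, so whether a raised value is recorded at all is judged by someone who knows the arm. That follows from the open design rather than from the scale, but a fixed threshold would reduce it.

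**Working it through.** The protocol states no figure to reproduce. The check applies the scale as written.

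**Step 1: is a raised enzyme value an adverse event?** Yes, if it is clinically relevant and is a worsening from baseline (5.2.2). AST and ALT have scheduled values at day 0 and day 7 (5.2.1), so a change can be observed.

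**Step 2: which grade does it get in a patient without symptoms?**

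| Grade | What the wording needs | Met by a symptom-free rise? |
|---|---|---|
| MILD | discomfort noted, activities not disrupted | second part only; no discomfort is noted |
| MODERATE | discomfort that affects activities | no |
| SEVERE | activities not possible | no |

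The value itself appears in no row, so the result is the same at any size: MILD on a generous reading, no grade on a literal one. No other section grades a laboratory value by its size.

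**Step 3: where does the event appear in the analysis?**

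- MODERATE and SEVERE rows of the 10.4.2 comparison: never.
- MILD row: yes, if the investigator assigns that grade; no, if it is left ungraded.
- Number of adverse events, which is what the named test compares: yes, in either case.
- Biochemical comparison: yes under the synopsis; not named in 10.4.2.
- Immediately reportable events: possibly, under 5.2.3, without changing the severity grade.

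**Step 4: illustration on assumed rates.** The protocol gives no expected rate of enzyme rises. Suppose 5% of one arm and none of another have a large silent ALT rise: 0.05 × 110 = 5.5, so 5 or 6 patients against 0.

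- As graded now, these events add 0 against 0 to the SEVERE row and 5 or 6 against 0 to the total. They add the same to the MILD row if graded MILD.
- Under a size-based scale that classed them as SEVERE, that row would read 5 or 6 against 0. The two-sided Fisher probability is twice the chance that all the events fall in one named arm of two arms of 110.
 - 5 events: 2 × (110/220 × 109/219 × 108/218 × 107/217 × 106/216) = 2 × 0.0298 = 0.060.
 - 6 events: 2 × (0.0298 × 105/215) = 2 × 0.0146 = 0.029.

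Under this assumption, a contrast near the conventional 0.05 level would be absent from the SEVERE row while remaining in the event total, where it is mixed with clinical complaints.

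**The case against.** The strongest reply is that little is lost. The event still counts in the number of adverse events, which is what the only named test compares. The synopsis lists laboratory values as a tolerance parameter and plans to compare biochemical results, which needs no grade. A hazardous value can be reported as an immediately reportable event, and 5.2.3 itself separates severity from seriousness. Detailed laboratory cut-offs are also often left to an analysis plan or laboratory manual.

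Most of this stands and sets the size of the point. Three qualifications remain.

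- The biochemical route is uncertain, because 10.4.2 names only haematology where the synopsis names both.
- Immediate reporting does not alter the grade and covers only the defined treatment period. If that means the dosing period, Lariam lasts 24 hours and quinine 5 days (section 5.1.1.3), so the day-7 sample falls outside it in both comparator arms.
- The point is not that something was left out. The protocol states a grading rule and applies it to events that it does not fit. Investigators record those grades during the trial, and a later analysis plan cannot recover size from them, although it could use the raw values.

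Two stronger readings are tempting but unsupported. A reader might infer that the reverse error also occurs and that a patient disabled by malaria is automatically a SEVERE event. Section 5.2.2 defines an event as an adverse change from the signs and symptoms at baseline, so incapacity already present at entry is not an event; only worsening is. A reader might also infer that the safety comparison is blind to liver toxicity and that its conclusion will favour the drug at fault. The other routes above contradict the first part. The second needs a difference between arms that no figure in the protocol supports.

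**Conclusion.** The point holds in a limited form and is of low priority. As written, the severity scale cannot grade a symptom-free AST or ALT rise above MILD, and read literally cannot grade it at all. The comparison by severity therefore cannot show such events as moderate or severe, however large they are. This follows from the wording alone and needs no numerical assumption.

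The effect on the trial's conclusion is conditional. It matters only if large silent rises occur, differ between arms, and are not picked up through the raw biochemical values. The 5% illustration is an assumption that serves only to show what happens in the SEVERE row; it is not an estimate for any of the three treatments.

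**What to change.** In section 5.2.2, keep the activity scale for clinical events and add a short table that grades AST and ALT events by size. Express size as a multiple of one reference, either the patient's own day-0 value or the laboratory's upper limit. The sponsor should fix the reference, the grade cut-offs and a single reporting threshold before enrolment and apply them alike in all three arms. The protocol offers no cut-offs, so none are suggested here.

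In section 10.4.2, tabulate laboratory events by grade separately from clinical events. Reconcile its restriction to haematological parameters with the synopsis, which also lists biochemical results.

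The proposal is confined to AST and ALT because 5.2.1 schedules both a baseline and a follow-up value for them; it lists haemoglobin at day 14 only.

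The cost is one grading table and one additional safety table. The day-0 and day-7 values are already collected, so no extra sample or visit is needed.
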